# The ACTIVE (Acute Cholecystitis Trial Invasive Versus Endoscopic) study: Multicenter randomized, double-blind, controlled trial of laparoscopic (LC) versus open (LTC) surgery for acute cholecystitis (AC) in adults

**DOI:** 10.1186/1745-6215-9-1

**Published:** 2008-01-10

## Abstract

**Background:**

In some randomized trials successful laparoscopic cholecystectomy for cholecystitis is associated with an earlier recovery and shorter hospital stay when compared with open cholecystectomy. Other studies did not confirm these results and showed that the potential advantages of laparoscopic cholecystectomy for cholecystitis can be offset by a high conversion rate to open surgery. Moreover in these studies a similar postoperative programme to optimize recovery comparing laparoscopic and open approaches was not standardized. These studies also do not report all eligible patients and are not double blinded.

**Design:**

The present study project is a prospective, randomized investigation. The study will be performed in the Department of General, Emergency and Transplant Surgery St Orsola-Malpighi University Hospital (Bologna, Italy), a large teaching institutions, with the participation of all surgeons who accept to be involved in (and together with other selected centers). The patients will be divided in two groups: in the first group the patient will be submitted to laparoscopic cholecystectomy within 72 hours after the diagnosis while in the second group will be submitted to laparotomic cholecystectomy within 72 hours after the diagnosis.

**Trial Registration:**

TRIAL REGISTRATION NUMBER ISRCTN27929536 – The ACTIVE (Acute Cholecystitis Trial Invasive Versus Endoscopic) study. A multicentre randomised, double-blind, controlled trial of laparoscopic versus open surgery for acute cholecystitis in adults.

## Introduction

In the developmental stage of laparoscopic cholecystectomy it was considered 'unsafe' or 'technically difficult' to perform laparoscopic cholecystectomy for acute cholecystitis [1,2]. With increasing experience in laparoscopic surgery, a number of centers have reported on the use of laparoscopic cholecystectomy for acute cholecystitis, suggesting that it is technically feasible but at the expense of a high conversion rate, which can be up to 35 per cent [3,4] and common bile duct lesions [5].

Several randomized studies in the early 1980s had shown that performing early open cholecystectomy for acute cholecystitis was better than delayed cholecystectomy in terms of shorter hospital stay but both had similar operative morbidity and mortality rates [3]. Early surgery had since gained in popularity in the late 1980s [2]. Routine use of the open procedure might enable more patients to have the operations during the acute phase because most surgeons are practiced in this approach. The impact of hospital stay and morbidity must also be taken into account. There is the expectation that open operation is associated with more pain and longer hospital stay [6-8].

In some trials successful laparoscopic cholecystectomy during the period of acute inflammation is associated with an earlier recovery and shorter hospital stay when compared with open cholecystectomy [8]. Other studies did not confirm these results and the potential advantages of early laparoscopic cholecystectomy can be offset by a high conversion rate to open surgery [5]. Moreover in these studies a similar postoperative programme to optimize recovery comparing laparoscopic and open approaches was not standardized. Many studies also do not report all eligible patients and are not double blinded.

## Methods

### Design

The study project is a prospective, randomized investigation. The study will be performed in the Department of Emergency Surgery St Orsola-Malpighi University Hospital (Bologna, Italy), a large teaching institutions, with the participation of all surgeons who accept to be involved in (and together with other selected centers).

The patients will be divided in two groups: in the first group the patient will be submitted to early LC (Laparoscopic Cholecystectomy) within 72 hours after the diagnosis of cholecystitis while in the second group will be submitted to early LTC (LaparoTomic Cholecystectomy) within 72 hours after the diagnosis.

#### Randomization

The randomization will be obtained through computer-generated schedule. The result of this randomization will be sealed in numbered envelopes. After cholecystitis diagnosis if the patient fulfils the inclusion criteria the responsible surgeon will ask the patient to partecipate to the study. If the patient agree, he/she will sign the informed consent. After patient's consent the randomization will be carried out. The responsible surgeon will record the patient name (and number). All eligible patients will be recorded.

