#### Data Collection

Patients' data sheets are generated containing demographic data and preoperative, operative, and postoperative information.

Pre-operative notes concern the history of gallbladder stones, the presence of associated diseases (cardiac, hypertension, diabetes, malignancy), duration of gallbladder complaints (as an indication for the onset of the disease), finding of a palpable gallbladder, temperature, and laboratory results of WBC count, serum bilirubin, gamma GT, PCR, IL-6 and alkaline phosphatase. Ultrasound findings are also reported.

Operative data of concern are macroscopic findings (of acute cholecystitis, gangrenous cholecystitis, hydrops, and empyema of the gallbladder), the presence of small stones (< 1 cm diameter) or large bile stones (> 1 cm diameter), information regarding perforation of the gallbladder and intraperitoneally "lost" stones, reasons for conversion, and duration of surgery. Postoperative notes of interest included the use of nasogastric tubes and drains, the amount of analgesics used, (evaluation of pain with VAS score), complications, and length of hospital stay.

Complications are classified as surgical infections (wound infection, subphrenic or subhepatic abscess); noninfectious surgical problems (e.g., bile duct injury, hemorrhage); remote infections (urinary or respiratory); and miscellaneous problems (e.g., atelectasis, deep vein thrombosis, AMI, CVA, etc). The collected information are entered into a database as either continuous or categorical variables for statistical analysis. Following the operative procedure, a large sterile dressing will be applied to cover the entire abdomen.

A second surgical team, aware of the operative findings but not the surgical access approach, then will assume the care of the patient. Postoperative care and ability to be discharged from the hospital will be determined by the second surgical team. This second surgical team will be blinded to the surgical approach. The primary operative team will be in every moment available for emergent consultation or evaluation of the wound.

In the pre-anaesthetic holding area, baseline pain will be investigated at rest and on coughing using a pain-rating scale systems: a 100-mm visual analogue scales (VAS) (0 = minimal and 100 = maximal).

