### Primary Endpoints

The aim of the study is to compare the results of early laparoscopic and laparotomic cholecystectomy for acute cholecystitis in terms of morbidity, mortality, conversion rate, operation time, hospital stay, postoperative pain, return to normal activity and aesthetic result.

The primary endpoints of our study will be:

To evaluate the value of laparoscopic cholecystectomy to reduce hospital stay

To evaluate the value of laparoscopic cholecystectomy to reduce postoperative pain

To evaluate the conversion rate

The onset of any other complications will be recorded intraoperatively, postoperatively, at discharge, at 7-days, 1-month and 6-months.

All the above mentioned data will be recorded in the Case Report Form and later stored in computer database. At the end of the study the final statistical examination will be carried out.

An interim statistical examination of the data will be done every 3 months during the period of patients' inclusion in the study. Then at the end of every completed follow-up period (1-month, 6-months).

The statistical analysis will be carried out using Epi Info 2000, Version 1.1 software package (Dean AG, Arner TG, Sangam S, Sunki GG, Friedman R, Lantinga M, Zubieta JC, Sullivan KM, Smith DC. Epi Info 2000, a database and statistics program for public health professionals for use on Windows 95, 98, NT, and 2000 computers; Centers for Disease Control and Prevention, Atlanta, Georgia, USA, 2000)

No incentives are planned for the patients regarding the operation or the follow-up.

The study will take approximately 6 months – 1 year for the inclusion period. According to the number of AC menaged monthly in all Centers, the duration of the inclusion period can be approximately of 1 year to reach the number of about 144 enrolled patients.

An interim report is planned at the end of any completed follow-up period.

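### Randomisation is tied to consent rather than to the start of the operation, and no masking is described for the interval before surgery, although the trial is called double-blind and pain is a primary endpoint

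*Protocol article*

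**What the plan says.** Randomization (Protocol article) sets the order: diagnosis, eligibility check, consent, allocation. At the consent step "the responsible surgeon will ask the patient to partecipate to the study"; then "After patient's consent the randomization will be carried out". The concealment device is stated: "The result of this randomization will be sealed in numbered envelopes". When an envelope is opened, by whom, and who then learns the arm are not stated.

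Design gives both arms the same window. For the laparoscopic arm the text reads: "the patient will be submitted to early LC (Laparoscopic Cholecystectomy) within 72 hours after the diagnosis of cholecystitis". The open arm has the same limit. The window runs from diagnosis.

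The title and the Trial Registration entry call the trial double-blind. The measures behind that label are in Data Collection: a large abdominal dressing put on after the operation; a second team that then takes over care and decides on discharge ("This second surgical team will be blinded to the surgical approach"); and a blinded investigator who scores pain from the return to the ward onwards. Baseline pain is scored in the holding area before anaesthesia.

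Primary Endpoints lists hospital stay ("To evaluate the value of laparoscopic cholecystectomy to reduce hospital stay"), postoperative pain and conversion rate. Statistics sizes the trial on hospital stay alone. No start point for the count is given; Data Collection lists it among the postoperative notes.

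**The concern.** The trigger for allocation is consent, not arrival in theatre or induction. As written, a patient can be allocated and then wait for surgery with nothing described that keeps the arm from the patient or the ward. The dressing and the change of team can protect only what has not already become known.

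Pain is the endpoint most exposed. The patient supplies the VAS score, so a patient who has learned the arm before surgery is unblinded for it, however well the assessor and the wound are masked. On the stated order the baseline VAS is also taken after allocation, so it is not clearly a pre-randomisation measurement.

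Hospital stay is exposed conditionally. If the count starts at admission, any difference between arms in the wait for surgery becomes part of the measured difference, although it is not an effect of the technique on recovery. The Introduction gives some reason to think such a difference possible: it suggests that routine open surgery might let more patients be operated on in the acute phase, because most surgeons are practised in it.

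**Working it through.** **Timeline, set side by side**

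| Step | Section | Masking described |
|---|---|---|
| Diagnosis; the 72 h window starts | Design | none needed |
| Consent, then randomisation | Randomization | sealed envelope; opening time not stated |
| Wait for surgery, at most 72 h minus the time from diagnosis to randomisation | Design, Randomization | none |
| Baseline VAS in the holding area | Data Collection | none |
| Operation | Intervention | not possible for the operators |
| Dressing, second team, blinded pain scoring | Data Collection | yes |

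The gap in masking follows from the order of steps and needs no arithmetic.

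**What an arm-dependent wait could do to hospital stay (illustration)**

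Inputs from Statistics: 72 per group, 144 in all; power 80%; significance level 0.05. Assumptions: two-sided test; the 2 days read as the target difference (the sentence is ambiguous); stay counted from admission; normal approximation.

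1. No SD is given, so 144 cannot be reproduced from the article. Solving backwards: SD = 2 / [(1.960 + 0.842) × √(2/72)] = 2 / (2.802 × 0.1667) = 4.28 days. This SD is what the assumptions imply; it is not a protocol figure.
2. Standard error of the difference: 4.28 × 0.1667 = 0.714 day.
3. Let b be the difference between arms in mean wait. With no true effect, type I error = 1 − Φ(1.96 − b/0.714) + Φ(−1.96 − b/0.714). For b = 0.5, b/0.714 = 0.70, and the sum is 0.104 + 0.004 = 0.108.
4. With a true 2-day benefit and the extra wait falling on the laparoscopic arm, power is about Φ((2 − b)/0.714 − 1.96). For b = 0.5 this is Φ(2.10 − 1.96) = 0.556.

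| b (days) | Share of 2 days | Type I error | Power, wait on laparoscopic arm | Power, wait on open arm |
|---|---|---|---|---|
| 0 | 0% | 5.0% | 80% | 80% |
| 0.25 | 12.5% | 6.4% | 68.8% | 88.3% |
| 0.5 | 25% | 10.8% | 55.6% | 93.8% |
| 1.0 | 50% | 28.8% | 28.8% | 98.8% |

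5. If stay is counted from surgery, b does not enter the endpoint and this direct bias is zero.

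All values of b are assumed. Nothing in the article indicates which of them, if any, would occur.

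**The case against.** The strongest reply is that the article states an order, not a time. Randomising after consent is correct practice, and the sentence is compatible with an envelope opened in theatre. A condensed article may leave the moment of opening to the full protocol. The roles it expressly blinds are the second team and the pain investigator; both act after the operation, and nothing says that the second team sees the patient beforehand. The operators' knowledge of the arm is unavoidable.

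Much of this stands, and it rules out several stronger readings that a reader might infer:

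- That the arm is revealed at consent, up to 72 h before surgery. The opening time is not given, and 72 h from diagnosis is only an upper bound on the interval.
- That theatre lists or booking unmask patient and ward. Neither is mentioned; this is a plausible route, not a documented one.
- That the measured stay includes the preoperative wait. Its place among the postoperative notes points, if anything, the other way.
- That the wait will differ by half a day or a day. Both arms share the same ceiling, and Intervention states one operator requirement without distinguishing arms, which weakens the argument from surgeon availability.

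Two parts of the reply do not carry. The article does fix the trigger for allocation, and it ties it to consent. It also claims double-blinding while describing protections that all start later. The patient is not named as a blinded party, but the label and a dressing over the whole abdomen make little sense otherwise, and the patient is the source of the pain score.

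Later opening would not remove the exclusion for a different pathology found at operation (Inclusion And Exclusion Criteria), which would still come after allocation.

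**Conclusion.** The point holds in a limited form. The stated sequence allows allocation to precede surgery by up to just under 72 h, and no masking of patient or ward is described for that interval. This conclusion rests on the text alone. It bears mainly on pain, which is patient-reported and primary, and on the baseline pain score.

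The effect on hospital stay is conditional: it needs a count from admission and a wait that differs by arm. The article establishes neither. The Introduction hints at a direction (open surgery easier to provide early) but gives no size. The 10.8% and 28.8% error rates show sensitivity under an assumed SD of 4.28 days and assumed differences of 0.5 and 1 day; they are not estimates of bias in this trial.

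The absence of a start point for stay would, on its own, be detail that the full protocol may supply. It matters here because of the gap between allocation and surgery. The change is worth making: opening the envelope later is cheap and less prone to bias than the stated sequence.

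**What to change.** - Take consent on the ward, but open the next numbered sealed envelope only in theatre, just before incision. Write the patient identifier and the time on the envelope before opening it.
- Book the case under a label that does not name the approach. Baseline pain is then measured before allocation, and patient and ward cannot learn the arm before surgery because it has not been assigned.
- Define the primary stay measure as running from the end of surgery to discharge as decided by the blinded second team. Report total stay from admission as secondary.
- Report the time from diagnosis or admission to surgery by arm, so that any imbalance is visible.
- Confirm that the SD behind 144 applies to the stay measure chosen, since the article gives none.

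Cost: instrument sets for both approaches must be ready in theatre for every case, although open instruments must be available anyway for conversion. One time field is added to the CRF, and the wording of Randomization and Primary Endpoints changes. The endpoint definition should be settled before any outcome data are examined, because interim examinations are planned every 3 months.

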### Statistics

Sample size has been calculated to reach a confidence level of 95% with a power of 80%.

A sample size of 144 patients is calculated supposing that the hospital stay for LC is shorter than 2 days. The sample size will be 72 patients for each group (144 patients for the whole study).

For comparison of the two groups, chi-square analysis and Fisher's exact test are used when appropriate for qualitative data, and the Student t-test (for normal variables) or the Mann Whitney U-test (for nonnormal variables) for quantitative data. For multivariate analysis the stepwise logistic regression is applied. A probability of 0.05 or less is accepted as statistically significant.

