### Inclusion And Exclusion Criteria

Inclusion criteria are:

Adult patients (>18 years)

Clinical (pain, fever > 37.5°C, WBC > 10.000/microL), and ultrasound evidence of cholecystitis

ASA I-III patients

Informed consent

Less than 72 h from the onset

Exclusion criteria

Informed consent refusal

Choledocholithiasis

Generalized peritonitis

Previous abdominal surgical procedures

Patients with an intra-operative findings of different pathology will be excluded from the study

Apache II score > 10

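### Hospital stay, the endpoint behind the sample size, is compared without covariates; a prespecified adjusted analysis on a scale suited to skewed days would add precision cheaply, although the stated tests are valid

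*Protocol article*

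**What the plan says.** All references are to the protocol article.

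- **Endpoint.** Under Primary Endpoints, the first of three items is "To evaluate the value of laparoscopic cholecystectomy to reduce hospital stay".
- **Size.** Statistics gives "A sample size of 144 patients is calculated supposing that the hospital stay for LC is shorter than 2 days", then "The sample size will be 72 patients for each group (144 patients for the whole study"). The basis is "Sample size has been calculated to reach a confidence level of 95% with a power of 80" per cent.
- **Test.** Quantitative outcomes are compared with "the Student t-test (for normal variables) or the Mann Whitney U-test (for nonnormal variables) for quantitative data", and "A probability of 0.05 or less is accepted as statistically significant".
- **Multivariable method.** Statistics names only stepwise logistic regression, without an outcome, a covariate list or a role.
- **Baseline data.** Intervention lists demographics, comorbid conditions and symptom history. Data Collection adds associated diseases, temperature, WBC, PCR, IL-6, liver tests and "duration of gallbladder complaints (as an indication for the onset of the disease").
- **Known at entry.** Inclusion And Exclusion Criteria admits "ASA I-III patients" and excludes an APACHE II score above 10, so both must be assessed for every candidate.

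**The concern.** With 72 patients per arm, any spread in stay that baseline severity or comorbidity could explain is left in the error term of a t-test or in the ranks of a Mann-Whitney test. This widens the interval for the treatment difference. A chance imbalance in severity between the arms also enters the estimate unadjusted, and the Randomization section mentions no stratification that would limit it.

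The logistic regression does not fill the gap. It models a categorical outcome rather than days, it lets the data select the covariates, and it is not tied to hospital stay. No stated analysis of stay therefore uses the baseline data. At stake are some points of power and some width of the confidence interval, at no cost in patients.

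**Working it through.** **1. Inputs.** From Statistics: 72 per arm, 5% significance, 80% power. Assumed: a two-sided test (sidedness is not stated), and the phrase about 2 days read as a difference of 2 days between the arms. No SD of stay is given.

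**2. The plan's own figure.** Without an SD, 144 cannot be reproduced. It can only be solved backwards:

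SD = 2 / [(1.960 + 0.842) × √(2/72)] = 2 / 0.467 = 4.28 days.

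The standardised difference is 0.467 (0.470 with the t distribution). Putting 4.28 back in returns 72 per arm, but that is circular. The power results in steps 3 and 4 need only the standardised difference. The widths in days also need the 2-day reading.

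**3. Gain from adjustment, normal model.** If the covariates explain a share R² of the variance in stay, the residual SD is 4.28 × √(1 − R²), and

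power = Φ(2.8016 / √(1 − R²) − 1.960).

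- R² = 0.10: 2.953 − 1.960 = 0.993, power 84.0%.
- R² = 0.20: 3.132 − 1.960 = 1.172, power 87.9%.

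The unadjusted standard error is 4.28 × √(2/72) = 0.714 days. The 95% half-width is 1.96 × 0.714 × √(1 − R²), and the equivalent unadjusted trial has 144 / (1 − R²) patients.

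| R² (assumed) | Power | 95% half-width, days | Equivalent unadjusted N |
|---|---|---|---|
| 0 | 80.0% | 1.40 | 144 |
| 0.05 | 82.0% | 1.36 | 152 |
| 0.10 | 84.0% | 1.33 | 160 |
| 0.20 | 87.9% | 1.25 | 180 |
| 0.30 | 91.8% | 1.17 | 206 |

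**4. Cost of estimating the covariates.** Five covariates reduce the degrees of freedom from 142 to 137 and inflate the variance by about 1 + 5/136 = 1.037. With the t-based difference of 0.470, the noncentrality 0.470 / √(2/72) = 2.82 becomes 2.82 / √[1.037 × (1 − R²)]. Power is then 78.5% at R² = 0, 80.2% at 0.04, 82.2% at 0.09, 85.1% at 0.16 and 88.8% at 0.25. Break-even is near R² = 0.04, and a 5-point net gain needs R² of about 0.16.

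**5. Skewed stay.** Length of stay is usually right-skewed, in which case the plan's own rule leads to the Mann-Whitney test, and that is the comparator to beat. Simulations at 72 per arm, with skewed stay assumed, gave:

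| Analysis | Power | Mann-Whitney, same setting |
|---|---|---|
| Adjusted linear model of raw days, robust errors, R² ≤ 0.10 | 78–83% | 85–90% |
| Adjusted linear model of log days, R² = 0 | 84–88% | 85–88% |
| Adjusted linear model of log days, R² = 0.20 | 90–94% | 84–90% |

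Adjustment helps here only if the scale suits the skewness.

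**6. What may hold R² down.** The entry criteria require fever above 37.5 °C, WBC above 10,000 per microlitre and less than 72 hours from onset, and they cap APACHE II at 10. WBC, duration of complaints and APACHE II, all candidate covariates, therefore have a restricted range.

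**The case against.** **Validity.** Randomisation makes the unadjusted tests valid, and their error rate and intervals already allow for chance imbalance. This stands in full: nothing in Statistics is wrong or contradictory on this point.

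**A condensed article.** Covariate lists are commonly left to the full plan. That is fair for the list itself, but the article does state the test for quantitative data, and that choice is open to comment.

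**Size of the gain.** A reader might infer that much of the spread in stay must be explained at baseline, because entry takes adults of any age in ASA I to III, and discharge depends on absence of fever and of illness needing hospital care. The documents do not support this. Fever, WBC and time from onset are narrowed at entry. The discharge criteria also include bowel function and the patient's compliance, and absence of fever at discharge is a postoperative state. No correlation with stay is given anywhere.

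**A free gain.** A reader might also infer that adjustment can only help. It cannot be called free: with uninformative covariates about 1 to 2 points of power are lost under the normal model.

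**The remedy.** Replacing the stated tests with a linear model of raw days could lower power against the Mann-Whitney test when stay is skewed. This stands, and it determines the form of the fix.

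**Data availability.** ASA class is an entry criterion but is not named among the recorded data, so its presence in the database is an inference.

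**Conclusion.** The point holds as an inexpensive improvement, not as a flaw that threatens the result. Stay is the sizing endpoint, the stated comparison uses no covariates, and usable baseline data are collected or needed for entry. Under a normal model with 80% base power, adjustment gives about 84% at R² = 0.10 and 88% at R² = 0.20 before the cost in step 4, and loses about 1 to 2 points at R² = 0. R² is an assumption throughout, and the entry limits may reduce it. The figures also assume a two-sided test, and those in days rest on the back-solved SD of 4.28 and a 2-day difference.

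A reader might go further and call the planned analysis biased, or the trial underpowered because of it. The documents support neither.

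**What to change.** In Statistics, name a prespecified covariate-adjusted analysis as the main comparison of hospital stay:

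- **Scale:** one suited to skewed days, for example a linear model of log days, or a rank-based or proportional-odds model. For log days, define stay so that it is always above zero.
- **Terms:** treatment arm, always retained, plus a few covariates measured before randomisation, such as age, ASA class or APACHE II, WBC or PCR, and centre. Fix the list before any comparative data are seen.
- **Exclusions:** no stepwise selection, and no operative findings or conversion, which arise after randomisation.
- **Reporting:** the adjusted effect with its 95% confidence interval, and the mean difference in days, since the trial was sized in days.
- **Supportive:** keep the unadjusted t-test or Mann-Whitney test.

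The cost is a change of text, a few degrees of freedom, a stated rule for an occasional missing laboratory value, and a check that ASA class or APACHE II is entered on the Case Report Form. The main effect measure also changes with the scale, so its interpretation should be stated. No extra patients or visits are needed.
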